#### Number of Families

With a minimum expected sample size of 20 families per therapist being assessed before and after the implementation of TIPS, statistical power will be >90% to detect even small effect sizes (0.1<Cohen *d*<0.3) for the effectiveness outcomes (ie, change in wait times and change in families’ perceptions of service quality).

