### Participants

Participants will be recruited from study sites according to the following eligibility criteria:

Managers (n=20; one per site): managers, or their delegates, responsible for rehabilitation services at the site and members of the local leadership team, will participate in the coadaptation of TIPS to their site. Managers may contribute to their site’s monthly mentoring meetings; aid in the recruitment of therapists, parents, a therapist champion, and a parent-partner for their site; and complete site- or service-specific data collection instruments before and after the implementation of TIPS.Therapists (n=600 with 50% anticipated response; n=300): physiotherapists, occupational therapists, or speech-language pathologists providing outpatient pediatric rehabilitation services to children aged 0 to 12 years at each site are recruited via the managers and are interested in using FCT. Therapists will participate in the TIPS program, complete data collection instruments as prescribed, and aid in parent recruitment.Parents (n=20 per therapist with an anticipated response rate of 33%; n=2000 families per assessment time point): 1-time data collection will be undertaken with 2 samples (preimplementation and postimplementation samples) of parents or caregivers who received services (either in-person, virtually, or both) from at least one participating therapist in the previous 3 months.Therapist champion (n=20; one per site): a therapist selected based on their telehealth experience and on peer recognition within their organization. Therapist champions are members of the local leadership team participating in the coadaptation of TIPS to their site and will oversee the monthly mentoring meetings and agree to report on the implementation process after the implementation of TIPS.Parent or patient partner (n=20; one per site): parent or patient partners will primarily be recruited from family, parent, or patient advisory committees at the participating sites or, in the absence of such initiatives, from regional, provincial, or national patient engagement programs. As members of the local leadership team, parent or patient partners will participate in the coadaptation of TIPS to their site and could be called upon to contribute to their site’s monthly mentoring meetings.

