#### Number of Therapists

At the therapist level, implementation outcomes will be assessed 3 times during each period (before, during, and after the implementation of TIPS) for a total of 10 data collection time points. Assuming an autocorrelation of repeated measures of *r*<0.3, data collected from 300 therapists will provide >80% power to detect moderate effect sizes (Cohen *d*≥0.5), using a first-order autoregressive segmented regression model [75] and a global type I error level of 5%, accounting for multiplicity of outcome assessments (Šidák correction) [76].

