#### Data Collection

At the service level, the *site profile questionnaire*, completed by managers before and after the implementation, includes questions related to organizational readiness for eHealth [87] as well as clinically relevant *wait time indicators* (eg, the average service wait time for service) [88,89]. To estimate changes in wait times (before vs after), a confounder-adjusted analysis using generalized linear mixed effects models will use a log-link function to account for the typically right-skewed nature of time data. Estimated fixed (intervention) effects for the effectiveness outcomes will be reported with Šidák-corrected 95% CIs [76].

To evaluate changes in perceived service quality, the *family questionnaire* will be electronically distributed by managers or therapists to eligible families. It includes a sociodemographic questionnaire (eg, remoteness of location), and *Measurement of Processes of Care-20* (MPOC-20), a valid and reliable 20-item self-reported measure of parents’ perceptions of the extent to which rehabilitation services are family-centered [90]. It contains five scales: (1) enabling and partnership, (2) providing general information, (3) providing specific information about the child, (4) coordinated and comprehensive care for the child and family, and (5) respectful and supportive care; it is scored on a 7-point Likert response scale, which indicates the extent to which the service provider engaged in the behavior (1=not at all to 7=to a very great extent). Each scale yields its own score, and no total score is calculated. Data will be analyzed using generalized linear mixed effects models with nested random effects (families within therapists within sites) to control for the correlated nature of the data (ie, the possibility that families have responded once or twice to the MPOC-20) and to account for therapist and site cluster effects. Analyses will be conducted for each of the 5 MPOC-20 domains and controlled for the same confounding variables described in the analysis for objective 1, as well as for family-level variables (eg, sociocultural background, child’s age, and gender).

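### The family power statement counts 20 families per therapist as assessed, but the recruitment plan expects about 6.7 to respond, so >90% power fails at the bottom of the stated effect range

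*Protocol article*

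**What the plan says.** All references are to the protocol article.

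- **Participants, therapists:** "Therapists (n=600 with 50% anticipated response; n=300".
- **Participants, parents:** "Parents (n=20 per therapist with an anticipated response rate of 33%; n=2000 families per assessment time point". The same item describes two samples: "1-time data collection will be undertaken with 2 samples (preimplementation and postimplementation samples".
- **Number of Families:** the power statement opens "With a minimum expected sample size of 20 families per therapist being assessed before and after the implementation of TIPS" and concludes that "statistical power will be >90% to detect even small effect sizes (0.1<Cohen *d*<0.3". It names wait times and families' perceptions of service quality as the outcomes covered.
- **Effectiveness Evaluation, Data Collection:** "Estimated fixed (intervention) effects for the effectiveness outcomes will be reported with Šidák-corrected 95% CIs". The five MPOC-20 scales are analysed separately, in models that nest families within therapists within sites.
- **Number of Therapists:** the therapist calculation works with "a global type I error level of 5%, accounting for multiplicity of outcome assessments (Šidák correction". Number of Families states neither an alpha nor a multiplicity adjustment.

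**The concern.** The figure of 20 families per therapist appears in both sections with different meanings. In Participants it comes before non-response; in Number of Families it is the minimum number actually assessed. The power claim rests on the second meaning, while the stated total of 2,000 families rests on the first.

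At stake is how an MPOC-20 result will be read. If a scale shows no change, readers will set that against a claim of more than 90% power for very small effects, a claim that rests on three times as many families as the study expects. The claim also has to survive the multiplicity correction that the plan itself prescribes for these outcomes.

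**Working it through.** **Inputs from the article.** 300 therapists; 20 families per therapist; 33% response; 2,000 families per time point; effect range 0.1 to 0.3 SD; separate pre and post samples; Šidák-corrected 95% CIs; five MPOC-20 scales.

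**Inputs assumed.** Two-sided tests; SD of 1 on the d scale; independent families unless stated otherwise; a Šidák family of five tests (the MPOC-20 scales) or six (those plus wait time). The article does not give the number of tests.

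**Step 1. Which meaning of 20 fits the total?**
- As the number approached: 300 × 20 × 0.33 = 1,980, which rounds to 2,000. Per therapist, 2,000 / 300 = 6.67.
- As the number assessed: 300 × 20 = 6,000.
- Using all 600 therapists approached: 600 × 20 × 0.33 = 3,960, which matches neither.

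Only the first reproduces the stated 2,000. The power statement therefore uses 6,000 / 2,000 = 3 times the planned families.

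**Step 2. Formulae.** For n families per time point:
- SE = √(2/n)
- power = Φ(d/SE − z), where z is the two-sided critical value
- Šidák alpha per test = 1 − 0.95^(1/k): 0.0102 for k = 5 (z = 2.57) and 0.0085 for k = 6 (z = 2.63)
- effect with 90% power = (z + 1.28) × SE

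**Step 3. Reproduce the plan's claim at n = 6,000.** SE = √(2/6000) = 0.0183 and d/SE = 5.48 at d = 0.10. Power is 99.98% unadjusted, 99.8% with k = 5 and 99.8% with k = 6. The claim holds on its own input.

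**Step 4. Repeat at the planned n = 2,000.** SE = √(2/2000) = 0.0316 and d/SE = 3.16 at d = 0.10.

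| Alpha | Power, d = 0.10 | d = 0.12 | d = 0.15 | Effect with 90% power |
|---|---|---|---|---|
| 5%, unadjusted | 88.5% | 96.7% | 99.7% | 0.1025 |
| Šidák, 5 tests | 72.4% | 89.0% | 98.5% | 0.122 |
| Šidák, 6 tests | 70.2% | 87.8% | 98.3% | 0.124 |

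At d = 0.20 power exceeds 99.9% in every row.

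**Step 5. Families needed for 90% power at d = 0.10.** n = 2(z + 1.28)²/0.10², which gives about 2,102 per time point unadjusted and about 2,965 with Šidák over five tests.

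**Step 6. Sensitivity to clustering (assumed values; the article gives none).**
- *Therapist level.* With m = 6.67 families per therapist, intraclass correlation ρ and correlation c of therapist effects between periods, variance = (2/2000) × [1 + (m − 1)ρ − mρc]. For ρ from 0.01 to 0.10 and c from 0 to 1, power at d = 0.10 runs from about 71% to 92% unadjusted and from 48% to 78% with Šidák over five tests. Stable therapist effects cancel in the pre-post contrast, which is why some values exceed the independent-family figure.
- *Site level.* If the site-specific change has SD τ over 20 sites, SE = √(2/2000 + τ²/20). That is 0.0387 for τ = 0.1 and 0.0548 for τ = 0.2. With Šidák over six tests the effect with 90% power is (2.63 + 1.28) × SE, about 0.15 and 0.21.

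**The case against.** The strongest reply is that the error barely touches the conclusion. The stated range is open at 0.1, so d = 0.10 itself is not claimed. Unadjusted, 2,000 families reach 90% from d = 0.1025, and about 2,102 would suffice at 0.10, so the plan is about 5% short. A one-sided 5% test would give 93.5%. Families who respond twice and covariate adjustment could add precision, so the independent-family figure is not a ceiling. The article describes a type 3 hybrid focused mainly on implementation, the MPOC-20 is an effectiveness outcome, and Participants already gives the right total.

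Most of this stands, and it limits the size of the point. It does not remove it. The plan reports 95% CIs, conventionally two-sided, with a Šidák correction; under that rule the gap at d = 0.10 is nearly 20 percentage points and closes only at about 0.12. No reading makes both family counts true, and a later analysis plan could not do so.

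It also stands that leaving the alpha and clustering allowance out of a condensed article is not in itself an error. They matter here only because the figure has to be recomputed.

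**Conclusion.** The inconsistency is certain: the family power statement uses three times the number of respondents that the recruitment plan expects. Its effect on power is real but narrow. With independent families, the claim of more than 90% fails from just above 0.10 up to about 0.12 under Šidák (five or six tests assumed), and only up to 0.1025 without correction.

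Three stronger readings may tempt a reader, and the article does not support them:
- *The claim needs all 6,000 families.* It does not: with independent families, about 2,102 (unadjusted) or 2,965 (Šidák, five tests) per time point suffice at d = 0.10.
- *The family comparison is underpowered across the stated range.* Before clustering, more than 90% still holds from about 0.12 to 0.13 upward, with about 98% or more at 0.15.
- *The detectable effect is really 0.15 to 0.21.* Those values follow only from an assumed SD of 0.1 to 0.2 in site-specific change, for which the article gives no figure.

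This check concerns the MPOC-20 outcomes only. Wait times are reported by managers and were not assessed here.

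**What to change.** In Number of Families, replace the count of 20 assessed with about 6 to 7 responding families per therapist, about 2,000 per time point, so that it agrees with Participants. Restate the MPOC-20 effect detectable with 90% power at the Šidák-corrected alpha: about d = 0.12 with no clustering allowance. State the number of tests in the Šidák family and the clustering assumed. If a more cautious value is wanted, give it as a range under labelled assumptions, for example 0.15 to 0.21 for a site-specific change with SD 0.1 to 0.2.

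The cost is one corrected sentence and one recalculation. Design, recruitment and analysis do not change; the stated detectable effect becomes slightly less favourable.

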**Effectiveness evaluation**																									
	Service wait times: time from service eligibility to first scheduled appointment		Managers		✓																	✓			
	Perceptions of service quality: MPOC-20^o^		Parents		✓																	✓			
	Changes in service delivery: semistructured interviews		Managers, therapist champions, therapists, and parents																			✓			

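### The power above 90% stated for change in wait times is derived from family numbers, but wait times are reported by 20 site managers, so the figure is not supported for that outcome

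*Protocol article*

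**What the plan says.** Under Sample Size, Number of Families, the protocol article starts from a "minimum expected sample size of 20 families per therapist being assessed before and after the implementation of TIPS" and concludes that "statistical power will be >90% to detect even small effect sizes", with Cohen d between 0.1 and 0.3. It applies this "for the effectiveness outcomes (ie, change in wait times and change in families’ perceptions of service quality"). One figure thus covers both outcomes.

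The two outcomes have different sources. In Table 1 the row "Service wait times: time from service eligibility to first scheduled appointment" names managers as the participants, with one tick before TIPS and one after. The MPOC-20 row names parents. Data Collection under Effectiveness Evaluation places the wait-time indicators in the site profile questionnaire that managers complete before and after implementation, and illustrates them with "eg, the average service wait time for service". Participants gives 20 managers, one per site. The family questionnaire is described as holding sociodemographic items, the MPOC-20 and family costs; wait time is not mentioned.

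**The concern.** Power depends on the number of independent values that enter the comparison. For wait times these come from 20 sites, not from the families who answer a questionnaire about something else. The family count is not a stand-in for the number of waits either. Parents qualify by having received services from a participating therapist in the previous 3 months, so many may have finished waiting well before either assessment.

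Wait time appears in the study objective and in the effectiveness hypotheses. A reader who takes the power statement at face value could read a null wait-time result as evidence against a small effect, when the design may have had little chance of detecting one.

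**Working it through.** **Inputs from the protocol.** d between 0.1 and 0.3 and power above 90% (Number of Families); 300 therapists (Number of Therapists); "n=2000 families per assessment time point" (Participants); 20 sites with one manager each (Number of Sites; Participants); one wait-time report before and one after (Table 1); Šidák-corrected intervals for the effectiveness outcomes (Effectiveness Evaluation, Data Collection).

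**Assumed.** Two-sided alpha of 0.05 before correction; the pre-post correlation ρ between site values; the SD in which d is measured; the number of values per site; the number of outcomes in the Šidák correction.

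**Step 1: reproduce the stated figure.** Treat families as independent, n per time point. The noncentrality is d√(n/2).
- n = 2000, d = 0.1: 0.1 × √1000 = 3.16, power 88.5%. At d = 0.15 it is 99.7%, and from d = 0.2 about 100%.
- n = 20 × 300 = 6000, d = 0.1: power 99.98%.

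So a figure around or above 90% does follow from family numbers, with families as independent units. (Participants expects 33% of 20 families per therapist to respond, about 6.7, whereas Number of Families calls 20 the minimum expected.)

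**Step 2: use the unit that reports wait times.** For one value per site before and after, d in between-site SD units, and a paired t-test with 19 degrees of freedom:
- standardised paired difference dz = d / √(2(1−ρ)); noncentrality = dz × √20.
- Example, d = 0.3 and ρ = 0.8: dz = 0.3/0.632 = 0.474; noncentrality 2.12; power 52%.

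| ρ | d = 0.1 | d = 0.2 | d = 0.3 |
|---|---|---|---|
| 0 | 6% | 9% | 15% |
| 0.5 | 7% | 14% | 25% |
| 0.8 | 10% | 27% | 52% |
| 0.9 | 16% | 48% | 81% |
| 0.95 | 27% | 77% | 98% |

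**Step 3: what 90% power would need.** With 19 degrees of freedom the noncentrality must be 3.42, so dz = 3.42/√20 = 0.764.
- Correlation needed: ρ = 1 − 20d²/(2 × 3.42²), which is 0.991 at d = 0.1, 0.966 at d = 0.2 and 0.923 at d = 0.3.
- Detectable d = 0.764 × √(2(1−ρ)): 0.76 at ρ = 0.5 and 0.48 at ρ = 0.8.

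**Step 4: Šidák.** The number of outcomes is not stated. Counting six (five MPOC-20 scales plus wait time), alpha = 1 − 0.95^(1/6) = 0.0085 and dz for 90% power rises to 0.965. The detectable d is then about 0.97 at ρ = 0.5 and 0.61 at ρ = 0.8. Power at d = 0.3 falls to 8% (ρ = 0.5), 24% (ρ = 0.8) and 54% (ρ = 0.9).

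**Step 5: more favourable readings.**
- Three service-level averages per site, treated as 60 independent pairs: 12 / 33 / 63% at ρ = 0.5 and 23 / 67 / 95% at ρ = 0.8 for d = 0.1 / 0.2 / 0.3, uncorrected.
- d in units of the SD of individual waits, with m waits per site and period: the variance of a site's difference is 2[ICC(1−CAC) + (1−ICC)/m], where CAC is the cluster autocorrelation. At d = 0.1, ICC 0.3, CAC 0.5 and m = 100 give 11%; ICC 0.05, CAC 0.9 and m = 300 give 91%.

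**The case against.** The strongest reply is that no single power can be computed from the article. A reader might infer that the real power is about 7-50%. That range needs a correlation of 0.5-0.8, d in between-site SD units and exactly one average per site, and the documents fix none of these. At ρ = 0.9 the upper end is 81%, and with 60 independent pairs at ρ = 0.8 it reaches 95% at d = 0.3. The average is introduced only as an example, indicators are mentioned in the plural, and the questionnaire is not shown, so managers may supply finer data. This stands, and it rules out any unconditional figure.

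Two further readings are tempting but are not part of this point. One might fault the statement that the model will "use a log-link function to account for the typically right-skewed nature of time data", since a link shapes the mean and not the error distribution. The wording is loose, but the distribution is not named, an article may leave it to the analysis plan, and a log link can be paired with a skewed distribution. One might also infer that a calendar trend cannot be separated from TIPS. That is a different design question, and it is too strong as put: regions start 2 months apart, which gives some calendar spread within both periods, and confounder adjustment is planned.

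Finally, this is a hybrid type 3 study with implementation outcomes as primary, and intervals will be reported, which would show imprecision. That limits the consequences. It does not supply a basis for the stated power: under none of these readings is the figure derived from wait-time data.

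**Conclusion.** The point holds as a mismatch of unit. The power above 90% is computed from families and applied by name to an outcome that families do not report, and nothing else in the article supports it for wait times. This conclusion needs no outside assumption.

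Its size is conditional. With one average per site and d on the between-site scale, power across d = 0.1-0.3 is 6-15%, 7-25%, 10-52% and 16-81% at correlations of 0, 0.5, 0.8 and 0.9, before Šidák. To reach 90% even at d = 0.3, the correlation would have to be about 0.92 or more. Service-level data or an individual-level SD scale could raise power considerably, in favourable cases above 90%. The documents therefore show that the claim is unsupported for wait times; they do not show what the true power is.

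**What to change.** Limit the family-based power sentence to the MPOC-20. For wait times, add a separate statement of the detectable effect, based on the number of site or service values that managers will report, and give the assumed pre-post correlation, the SD scale of d, the number of outcomes and the resulting Šidák alpha.

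If the data are 20 site pairs, the statement would read: 90% power requires d of about 0.76 (correlation 0.5) or 0.48 (correlation 0.8) at alpha 0.05, and about 0.97 or 0.61 with Šidák for six outcomes, the count being an assumption to confirm. If managers will give service-level or individual waits, say so and base the calculation on those, allowing for clustering within sites.

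This costs a recalculation and a less favourable stated figure, with no change to the conduct of the study. Where sites already hold monthly wait-time averages, asking for them is an option, but whether sites can supply them is unknown and the correction does not depend on it.

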### Conceptual Framework

The structure of this study (Figure 2) builds on implementation science frameworks that aim to accelerate the translational research pipeline [72], bridging the current knowledge-to-practice gap. Specifically, the Consolidated Framework for Implementation Research [77] will guide the identification of factors influencing the adoption of FCT and will help engage leaders in participating sites in adapting the TIPS to their own contextual drivers, while maintaining the FCT key ingredients. A type 3 hybrid design will be used, primarily focusing on implementation indicators (bold text in Figure 2), while also collecting some effectiveness outcomes, with comparative assessments occurring at the therapist, service, or family level. This design is recommended when there is (1) momentum for implementation within the health care system, (2) strong face validity and indirect evidence for the clinical intervention and implementation strategy to support generalizability, (3) minimal risk associated with the clinical intervention and the implementation strategy, and (4) evidence of feasibility for the implementation strategy and support in the clinical and organizational context under study [72].

Data collection procedures are presented in Figure 2, and Table 1 presents an overview of the tools used and the participant groups involved. Details are provided in the next sections.

**Figure 2 figure2:**
[figure not shown]
Conceptual framework and key concepts as per implementation-effectiveness design. FCT: family-centered telerehabilitation; TIPS: training intervention and program of support.

**Table 1 table1:** Data collection measures, targeted participants, and time points.

Objective and measures				Participants		Time points																			
						Before TIPS^a^						During TIPS									After TIPS				
						T–3^b^		T–2^c^		T–1^d^		T0^e^		T1^f^		T2^g^		T3^h^		T4^i^			T5^j^		T6^k^
